#### B.6. Severity Assessment

The treating clinician or investigator will use the adjectives mild, moderate, or severe to describe the maximum intensity of the adverse event. For purposes of consistency, these intensity grades are defined as follows:

• Mild- Does not interfere with participant's usual function.

• Moderate- Interferes to some extent with participant's usual function.

• Severe- Interferes significantly with participant's usual function.

Note the distinction between the severity and the seriousness of an adverse event. A severe event is not necessarily a serious event. For example, a headache may be severe (interferes significantly with participant's usual function) but would not be classified as serious unless it met one of the criteria for serious adverse events, listed above.

#### B.7. Exposure In Utero

The license for NRT does not exclude use in pregnancy and NICE guidelines allow such use. We will exclude pregnant or breast feeding women because the dose and format of NRT advised for pregnant women is different from that used in our protocol. Consequently, we will adjust the dose of NRT should a woman become pregnant during treatment. As NRT use in pregnancy is routine in NHS practice, we will not follow up such women to determine the outcome of pregnancy in such cases.

#### B.8. Causality Assessment

The pharmacist's or investigator's assessment of causality must be provided for all adverse events (serious and non-serious). An investigator's causality assessment is the determination of whether there exists a reasonable possibility that the investigational product caused or contributed to an adverse event. If the investigator's final determination of causality is unknown and the investigator does not know whether or not investigational product caused the event, then the event will be handled as "related to investigational product" for reporting purposes. If the investigator's causality assessment is "unknown but not related to investigational product", this should be clearly documented in the CRF. In addition, if the investigator determines a serious adverse event is associated with trial procedures, the investigator must record this causal relationship, as appropriate, and report such an assessment in accordance with the serious adverse event reporting requirements, if applicable.

#### B.9. Evaluation of AEs for causality

• Not Related. Onset of the event as relative to administration of the product, is not reasonable; or, another cause itself can explain the occurrence of the event

• Unlikely to be related. Onset of the event as relative to administration of the product is possible but another cause itself can explain the occurrence of the event or there are no reasonable grounds for suspecting that the product could have caused the event.

• Possibly related. Onset of the event as relative to administration of the product is reasonable; however the event could have been due to another, equally likely, cause

• Probably related. Onset of the event as relative to administration of the product is reasonable and is more likely explained by the drug than by any other cause.

• Definitely related. Onset of the event as relative to administration of the product is reasonable and there is no other cause to explain the event; or a re-challenge (if feasible) is positive.

AE is classified as "not related" or "unlikely to be related" in case the patient has stopped using NRT seven days or longer at occurrence of the event.

The pharmacists/clinicians' responsibilities and processes for evaluating AEs

The participant will be encouraged to report AEs to the pharmacist, who will manage these in the normal manner for reported AEs. The pharmacist completes a form called: "Undiagnosed health problem or hospitalisation/death/disability log" in the CRF. In the case of SUSARs or SAEs, the pharmacist will report to the PI or other member of the investigating team within 24 hours of becoming aware of such a possible occurrence. In case the research team becomes aware of the occurrence first, the Principal Investigator will inform the pharmacist and fill in the log in the online CRF. It is pharmacist's responsibility to ensure that both versions of the CRF log (online and paper version) are accurate.

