### Behavioural support arms

#### Supported standard programme

The behavioural support schedule will follow that used in the Nicorette industry trials, providing support and monitoring at baseline, 2, 6, 10, 16, 22, 28, and 34 weeks. The pharmacist giving support in a consulting room will invite participants to set a treatment goal and provide advice on how to reduce cigarettes using unstructured or structured methods of smoking reduction. Unstructured smoking reduction means that participants were not guided as to which cigarettes to eliminate but are left to experiment themselves and without a specific goal except 50% reduction by 6 weeks. Structured reduction means having specific sequential goals for either reducing cigarettes per day or reducing smoking periods. The cigarettes per day methods are either smoke-free periods (SFP) or lengthen the inter-cigarette interval, i.e. the timer method [14,15]. Smoke-free periods concentrates on times when smoking is allowed and when it is not, but the number of cigarettes is not restricted. In the timer method the number of cigarettes per day is restricted and also times when smoking is allowed.

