#### Supported short programme

Participants in the 4-week supported programme will be given the same advice and help with reduction but this will be provided on a different schedule. Participants will be seen weekly for four weeks with the aim of reducing smoking to achieve cessation by the end of four weeks. If this fails, reducing to induce cessation at 8 weeks will be the goal. Thereafter, consistent with the pragmatic nature of this trial, participants in the short reduction arm will be allowed to follow the standard reduction regime. Behavioural support will be provided at baseline, weekly to 4 weeks, 6, 8, and 16 weeks i.e. the same number of visits but on a different schedule.

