### No support arms

Participants in the no support arms will not be given advice or support by the pharmacist. Instead they will be given a leaflet that describes the reduction programmes (unstructured, cigarettes per day, or smoking periods) and which gives brief advice on using one or more of these approaches, and encourages use of NRT to support this. Participants will be advised to reduce on a schedule that follows the standard programme, if randomised to that arm, or the short programme, if randomised to that arm. The leaflet will advise participants to return to the pharmacy for more NRT to support reduction as needed. This will be dispensed on NHS prescription (following the primary care trust's patient group direction). The outcomes will be monitored without personal visits to avoid the possibility that these are contributing to adherence to the programme.

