### Trial Outcomes

This is a pilot trial designed to test the processes, examine implementation issues, and reactions to the programme of those involved i.e. whether pharmacists can be trained to implement the reduction programme, how well they do so, and how this is received by smokers and by pharmacists. These processes will be measured by:

• The percentage of pharmacists that agree to participate and the percentage that are trained and pass an assessment of competence.

• The monthly recruitment rate of patients into reduction programmes and into NHS stop smoking programmes, comparing the rate of recruitment into stop smoking programmes for pharmacists participating in the trial with those not doing so.

• Recording of some consultations and analysing their content against the schedule of proposed content.

• The proportion of people that would recommend the smoking reduction programme to another smoker and their views on the way that it ran, taken from the 12 month evaluation questionnaire.

We will also examine whether behavioural support is more effective than no support and will investigate whether shorter reduction programmes are more effective than standard length reduction programmes. This will be achieved by measuring self-reported sustained smoking reduction and abstinence. Smoking cessation outcomes will be measured from the time of quitting and we will measure 4 week and 6 month prolonged abstinence following the Russell standard, i.e. by intention to treat and biochemically confirmed [12]. Thus abstinence will be defined as allowing a two week grace period after quit day in which smoking lapses do not count against abstinence and from day 15 onwards, no more than five cigarettes have been smoked. This will be verified by a CO < 10 ppm. Smoking reduction will be assessed by the proportion of people that reduce their consumption to < 50% of baseline value, the mean cigarette consumption at the end of the trial.

As this is a preliminary trial, we will record data to allow us to assess whether the processes of the trial need improvement prior to a definitive trial. We will also examine data on adverse events and drop outs from the programme (Appendix 1).

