### Follow up procedures

We propose testing the feasibility of using a follow up method that is unlikely to be perceived by participants as providing them with behavioural support or enhance motivation to adhere. This will be by email/Webform emailed monthly for the 12 months of a participant's involvement in the trial. Monthly follow up will ensure that we can assess whether smokers have started their period of abstinence and schedule verification visits, based on a process outlined for trials of this kind [18]. Web follow up has achieved > 90% follow up in a previous trial [19]. Based on our experience of trials in smokers' clinics, most patients have email addresses and these are useful for follow up. Text reminders will be sent to participants registered for email follow up not responding to the email. For those not using a computer regularly, phone follow up by telephonists will be used so that the pharmacist/therapist is not conducting follow up.

Sustained smoking reduction will be measured as self-reported daily cigarette consumption at 12 month follow up, with a reduction being counted as self-reported consumption lower than at baseline. Sustained reduction will be counted as achieved if during the last four months (i.e. reports at month 9-12) of follow up, a person is smoking less at every follow up occasion than at baseline, measured by self-report. If a monthly report is missing, a person will be counted as having achieved sustained reduction if all other reports show this is the case and the last report is not missing. If two reports are missing, a person will be counted as not having achieved sustained reduction. Mean cigarettes per day at the end of follow up will be calculated from the last follow up only. If cigarettes per day is missing, then this will be replaced by baseline cigarettes per day, but in sensitivity analysis, we will use last observation carried forward.

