### Trial Medication

Participants are encouraged to use both a nicotine patch and a short-acting (acute) form of NRT and those who are eligible to pay a prescription charge on the NHS (£7.20) will have to do so for each item dispensed. Combination patch plus acute NRT is becoming a standard dosing regimen for cessation treatment [24], with manufacturers now packaging combined products. This is because of superior efficacy in enhancing cessation of combination over single form NRT [24]. There are fewer trials of NRT in smoking reduction, too few to assess the relative efficacy of the different NRT preparations [2], and no trials of combination NRT versus single form NRT. Therefore the dose regimen is based upon limited trial evidence and extension of the evidence from its use in cessation (reduction to zero cigarettes). A systematic review of placebo controlled short-term trials of nicotine patch and acute NRT show that both reduce daily cigarette consumption in people who are not trying to reduce their smoking and people who are [25]. Both patch and acute NRT appear equally effective in assessing reduction. One long-term trial allowed people free choice between patch, gum, and inhaler and found that gum produced the greater reduction of cigarettes than patch or inhaler [26]. The rationale for patch use is that smokers find regular use of the patch very easy, with typically very high levels of adherence [27], while acute NRT dosing is often sub-optimal [28]. However, acute NRT provides a direct behavioural replacement of cigarettes (such as 'have a piece of gum when you would ordinarily smoke') and this appears important in smoking reduction [29]. This population have relatively low interest in cessation and might need to continue pharmacotherapy for up to a year, so a combination approach seems most likely to produce optimal adherence to regimen and optimal efficacy.

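### Adverse events are captured mainly by spontaneous report to the pharmacist, whose scheduled contact differs by randomised arm, so comparing support with no support is open to ascertainment bias

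*Protocol article*

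**What the plan says.** All places are in the protocol article.

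- **Capture route.** Appendix 1, B.9: "The participant will be encouraged to report AEs to the pharmacist, who will manage these in the normal manner for reported AEs". The pharmacist then completes a log in the case report form. A second route covers events that reach the research side first: "In case the research team becomes aware of the occurrence first, the Principal Investigator will inform the pharmacist and fill in the log in the" (the sentence ends by naming the electronic case report form).
- **Scheduled contact, supported standard programme.** "providing support and monitoring at baseline, 2, 6, 10, 16, 22, 28, and 34 weeks".
- **Scheduled contact, supported short programme.** "Behavioural support will be provided at baseline, weekly to 4 weeks, 6, 8, and 16 weeks". The section describes this as equal in number to the standard programme, and lets participants move to the standard regime later.
- **Contact in the no support arms.** "The outcomes will be monitored without personal visits to avoid the possibility that these are contributing to adherence to the programme". A leaflet tells these participants to come back for further NRT when they need it. Under the dose alteration rules, pharmacists deal with problems in this group when a participant brings them.
- **Exposure.** All participants receive NRT (text to Figure 1). The Trial Medication section says this population "might need to continue pharmacotherapy for up to a year"; the section on initial patch dose speaks of nine months. B.2 defines the window for serious events by medication use plus a period of 7 or more days after stopping, not by visits.
- **Use of the data.** Trial Outcomes: "We will also examine data on adverse events and drop outs from the programme". The Statistics section compares outcome measures by arm descriptively, where that is judged sensible.
- **Contact common to all arms.** Follow up procedures: "This will be by email/Webform emailed monthly for the 12 months of a participant's involvement in the trial", with telephone calls for those who do not regularly use a computer. The section describes how smoking outcomes are derived and mentions no adverse event question.

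**The concern.** A spontaneous report needs an occasion. In the supported arms a participant sits down with the pharmacist seven times after baseline. In the no-support arms nothing is scheduled after enrolment. If the true risk of a recordable event were the same in all arms, the log would still be expected to hold more events from the supported arms, because they have more opportunities to mention one. A reader of the pilot could then take a difference in recording for a difference in harm.

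There is a safety side as well. Under the withdrawal criteria, a serious event judged related leads to withdrawal of the NRT prescription, and that can operate only if the event becomes known. Participants who manage their own NRT with no scheduled visit are those whose events are most easily missed.

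The designers saw that contact can influence outcomes and built an arm-neutral monthly follow-up for smoking status. As described, adverse events stay on the channel that depends on the arm.

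**Working it through.** **1. The plan's own figure.** The supported short programme is said to have as many visits as the standard one. Standard: weeks 0, 2, 6, 10, 16, 22, 28, 34, which is 8. Short: weeks 0, 1, 2, 3, 4, 6, 8, 16, which is 8. The statement is reproduced. The number of visits is equal; the timing and the last visit (week 34 versus week 16) are not. The no-support arms have 0 after enrolment.

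**2. Gap between the last scheduled visit and the possible end of NRT.** Both durations in the article are used as a range: nine months = 9 × 52/12 = 39 weeks, and one year = 52 weeks. Gap = end of NRT − last scheduled visit.

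| Arm | Last scheduled visit | Gap, 39 weeks of NRT | Gap, 52 weeks of NRT |
|---|---|---|---|
| Supported standard | week 34 | 39 − 34 = 5 | 52 − 34 = 18 |
| Supported short | week 16 | 39 − 16 = 23 | 52 − 16 = 36 |
| No support (both) | enrolment | 39 | 52 |

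These are gaps in scheduled contact only. Unscheduled pharmacy contact can fall within them.

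**3. What unequal capture could do.** The article gives neither event risks nor capture probabilities, so the following are assumptions shown as a range: the same true risk p in every arm, from 10% to 40%, and capture of 90% with support against 70% or 50% without. About 80 participants per level of the support factor comes from the text to Figure 1.

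- Recorded risk = p × capture. The spurious risk ratio is the ratio of the capture probabilities, whatever p is: 0.90/0.70 = 1.29 and 0.90/0.50 = 1.80.
- Spurious risk difference = p × (difference in capture). At 90% versus 70%: 0.10 × 0.20 = 2 points to 0.40 × 0.20 = 8 points. At 90% versus 50%: 0.10 × 0.40 = 4 points to 0.40 × 0.40 = 16 points.
- Chance that a two-sided 5% test, if someone ran one, would call this difference significant: Φ[(d − 1.96·√(2p̄(1 − p̄)/80)) / √((p₁(1 − p₁) + p₂(1 − p₂))/80)], where p₁ and p₂ are the recorded risks, d their difference and p̄ their mean. Example with p = 30% and 90% versus 50%: p₁ = 0.27, p₂ = 0.15, d = 0.12, p̄ = 0.21; the result is 46%. Over p = 10% to 40% it is 7% to 19% at 90% versus 70%, and 17% to 62% at 90% versus 50%.
- With equal capture (90% in both) the spurious difference is zero.

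**4. Whether the unscheduled contacts even this out.** Resupply in the no-support arms happens as needed and depends on continuing NRT. Someone who stops because of an adverse event has no resupply reason to return, although B.2 still counts serious events after stopping. When these participants do return, the section on transfer to the cessation programme has them asked about quit attempts; no question about harms is mentioned. Carbon monoxide verification reaches only those who report abstinence. The research-team route in B.9 says what happens once the team knows of an event, not how the team would come to know. These contacts reduce the imbalance but do not remove it systematically.

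**The case against.** Several stronger readings are tempting, and the article does not support them.

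- **That the pharmacist is the only route.** B.9 also provides for events the research team hears of first, and the research side is in monthly contact with every arm. That route is passive, but it exists.
- **That capture ends with the last visit.** Scheduled visits end; reporting does not. Participants still using NRT return to the pharmacy for supplies, some attend for carbon monoxide checks, and the window for serious events follows medication use.
- **That every comparison by arm is biased.** Short versus standard within the no-support arms involves no difference in scheduled contact. Within the supported arms the difference is in timing, not number. Serious events probably depend less on visits than others.
- **That a formal comparison of adverse events by arm is planned.** None is specified. The data are to be examined, in the context of whether trial processes need improving, and comparisons by arm are descriptive and conditional.
- **That the monthly form certainly omits safety.** The article does not list the form's items, and a condensed article may leave them to the full protocol.
- **That the bias is large.** Nothing in the article supports any particular capture rate. B.5 takes mild, expected events out of the pharmacist's log in every arm, so the remaining events may be reported more fully than a pessimistic assumption implies.

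It can also be said that light-touch safety capture is a reasoned choice for a well-established medicine, and that more questions each month could act as support. Both stand. The second bears on the design of the fix, because added contact is relatively greatest where there was none.

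None of this removes the core. Appendix 1 describes the adverse event process in detail and positively states a route whose opportunities depend on allocation.

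**Conclusion.** The concern holds in a limited form. As the plan is written, ascertainment of adverse events can be expected to differ between support and no support (8 scheduled contacts in each supported arm against none after enrolment). Scheduled contact also stops 5 to 18 weeks (supported standard) or 23 to 36 weeks (supported short) before NRT may stop. A raw comparison of support with no support is open to ascertainment bias, probably towards more recorded events with support.

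The counts and gaps follow from the article, given NRT use of 39 to 52 weeks. The direction is a judgement. The size cannot be computed: spurious risk ratios of about 1.3 and 1.8 are illustrations under assumed capture of 90% versus 70% and 90% versus 50%. The point does not touch the smoking outcomes or the sample size. It is worth correcting because adverse events are a stated output of a pilot for a definitive trial, and the correction is cheap.

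**What to change.** - Add one short, identically worded item to the monthly webform and telephone follow-up in all four arms, months 1 to 12: any new health problem or hospital attendance, and NRT use, since the last contact. If the full protocol or the form already has such an item, state it in the follow-up section and refer to it from B.9.
- Send positive answers to the research team and enter them in the B.9 log through the existing research-team route.
- Base any summary of adverse events by arm on this source. List pharmacist-reported events separately, without comparing support with no support.
- If the item cannot be added, report adverse events by arm descriptively and state that capture depended on contact.

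**Cost.** A protocol amendment and a slightly longer monthly contact. Since every arm receives NRT, the item need not reveal allocation to the blinded telephonists. The main downside is a small risk that the question is felt as attention or prompts adherence. That risk is relatively greater in the no-support arms and could slightly dilute the support contrast, so the item should be brief and neutral. No dose or clinical rule changes.

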#### B.10. The CI/PI's responsibilities and processes for evaluating AEs

Each AE reported to the PI will be evaluated for seriousness, causality, expectedness and severity. The responsibility for this will lie with [name], the PI..

Reporting to the sponsor will be required where the AE has a possible causal relationship to the trial intervention, and/or is unexpected. In this case [name] will report the event to the sponsor as soon as being made aware of the event. An initial verbal report can be made but will be followed promptly with a detailed written report on the trial SAE form The copy of the form will be filed in the trial master file.

Timeframes in which the Sponsor will submit expedited reports to the Research Ethics Committee (REC) and to the Medicines and Healthcare Products Regulatory Agency (MHRA)

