#### B.5. Monitoring and reporting adverse events

NRT is a well tried and tested medication and there are minor common and well known side-effects that it will not be practical or useful to record. For example, oral NRT almost universally causes burning in the mouth that most people find initially unpleasant but become used to in due time. Where adverse events are listed in SPC as expected and are classified as mild, pharmacists will not be required to record these on the adverse event form.

For all other adverse events (i.e. moderate or severe or possibly serious), the investigator will pursue and obtain information adequate both to determine the outcome of the adverse event and to assess whether it meets the criteria for classification as a serious adverse event requiring immediate notification to the sponsor, the NHS R&D office, and the research ethics committee. The investigator will assess causality. For adverse events follow-up by the investigator is required until the event or its sequela resolve or stabilise.

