##### B.10.1. *Fatal/life threatening SUSARs*

The sponsor will inform the REC of the above as soon as possible, but no later than 7 calendar days after he has first knowledge of the minimum criteria for expedited reporting.

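### Appendix 1 gives two different triggers for reporting an adverse event to the sponsor: seriousness in B.5, causality and/or expectedness in B.10

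*Protocol article*

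**What the plan says.** B.5 exempts events that are both mild and SPC-listed from recording. For the rest, the investigator must gather enough information for this step: "assess whether it meets the criteria for classification as a serious adverse event requiring immediate notification to the sponsor, the NHS R&D office". A further recipient is the ethics committee (REC). Nothing there depends on causality or expectedness.

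B.10 opens with "Each AE reported to the PI will be evaluated for seriousness, causality, expectedness and severity". The rule that follows is "Reporting to the sponsor will be required where the AE has a possible causal relationship to the trial intervention, and/or is unexpected". The next sentence ties the PI's report to that case. An initial verbal report is to be "followed promptly with a detailed written report on the trial SAE form".

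For the step before that, B.9 says "In the case of SUSARs or SAEs, the pharmacist will report to the PI or other member of the investigating team within 24 hours". The Withdrawal criteria section gives the same route. B.9 also has a fixed rule: an event that occurs seven days or longer after the patient stopped nicotine replacement therapy (NRT) is classed as unrelated or unlikely to be related. B.2 counts as serious adverse events (SAEs) those that arise during medication use or in a window afterwards, whose length it gives as seven or more days.

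The lead-in at the end of B.10 announces deadlines for expedited reports to both the REC and the MHRA. B.10.1 then reads "The sponsor will inform the REC of the above as soon as possible, but no later than 7 calendar days". B.10.2 names OXREC and B.10.3 names the REC. The Ethical approval section gives the approving committee as Birmingham East, North and Solihull.

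**The concern.** The PI is given two instructions for the same decision, and they can lead to different actions. B.5 looks only at seriousness. B.10 has seriousness evaluated but then leaves it out of the trigger.

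At stake is whether the sponsor sees every serious event, including those that the trial team has classified as unrelated. If B.10 is the rule used, the causality classification settles the matter for a listed serious event. B.8 adds to the difficulty: it sends serious events linked to trial procedures to the SAE reporting requirements, and the appendix holds two versions of these. The trial runs in 10 pharmacies with, by the Exclusion criteria section's own account, little clinical monitoring, so one unambiguous reporting rule matters.

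**Working it through.** No figure in the plan is involved, so the check sets the two triggers side by side over all combinations of three yes/no properties: 2 × 2 × 2 = 8.

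Readings used:
- *Related* means possibly, probably or definitely related in B.9. Unrelated and unlikely are taken as not meeting B.10's causal condition. For unlikely, this is a reading of the text.
- *Expected* means listed in the SPC, as in B.3 to B.5.
- B.10 applies once an event has reached the PI.

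| Serious | Related | Expected | B.5: notify sponsor immediately? | B.10: report to sponsor? |
|---|---|---|---|---|
| yes | yes | yes | yes | yes |
| yes | yes | no | yes | yes |
| yes | no | no | yes | yes |
| **yes** | **no** | **yes** | **yes** | **not required** |
| no | yes | yes | no | yes, read literally |
| no | yes | no | no | yes, read literally |
| no | no | no | no | yes, read literally |
| no | no | yes | no | no |

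The rules agree in 3 + 1 = 4 combinations and differ in 1 + 3 = 4. These are kinds of event, not numbers of events.

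**Can the serious conflict arise?** Yes. B.9 assigns events from seven days after stopping NRT to unrelated or unlikely by rule, while the B.2 window of seven or more days still counts them as SAEs if they are serious. B.9 also allows the unrelated category whenever another cause explains the event. If such an event is SPC-listed, it falls in the bold row.

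**Can the non-serious conflict arise?** Yes, for events that reach the PI. B.5 has the investigator pursue moderate and severe events. The Initial patch dose section lists vivid dreams and insomnia among the commonest side-effects of the patch. Moderate insomnia possibly due to the patch therefore meets B.10 as worded, with a written report on the SAE form, although B.5 asks for no immediate notification.

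**Recipients.** The B.10 lead-in names the REC and the MHRA. None of B.10.1 to B.10.3 names the MHRA, and the OXREC of B.10.2 does not match the committee in the Ethical approval section.

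**The case against.** A reader might infer that a serious, listed event judged unrelated never reaches the sponsor. The documents do not support that. B.10 says *where*, not *only where*, nothing makes it override B.5, and B.5 followed as written still sends the event. What remains is a contradiction and not a certain omission. It is a real one, because the sentence after the B.10 trigger ties the PI's report to the cases just named.

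B.5 could also be read as covering only those SAEs that require immediate notification. It gives no criterion for picking them out, so seriousness alone is the natural reading.

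The serious conflict is narrow, and this objection stands. B.8 treats unknown causality as related for reporting, the possibly related category already covers an equally likely other cause, and an unlisted serious event meets B.10 whatever its cause. Nor would the event be hidden: the pharmacist logs it in the paper and online case report forms and reports it to the PI or another team member.

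A reader might also infer that B.10 floods the sponsor with trivial unlisted illness. The stated route from pharmacist to PI covers SAEs and SUSARs, and the sponsor report goes on the SAE form, so a minor illness has no stated path to the PI. Only the looser point survives: B.10 says AE without saying whether non-serious events are meant.

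Finally, a reader might infer that a fatal SUSAR goes to the REC alone. The lead-in does name the MHRA, and the Ethical approval section commits the trial to the EU Clinical Trials Directive and ICH-GCP. This part is a drafting gap only.

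**Conclusion.** The concern holds as an internal contradiction in a safety-reporting rule. B.5 and B.10 give different triggers, and no other section says which governs. They differ in one of the four serious combinations (SPC-listed and judged unrelated or unlikely) and, on the literal wording of B.10, in three of the four non-serious ones.

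The number of events affected cannot be derived. The documents give no event rates, and an assumed rate for all SAEs would not size the one serious combination in conflict. The conclusion rests on reading B.5 as triggered by seriousness alone and on reading B.10 as stating when a report is required. It does not show that any event would be lost to the sponsor. It should be corrected because the wording is wrong as it stands and the correction costs almost nothing. The MHRA and OXREC points are minor.

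**What to change.** Reconcile B.5 and B.10 into one sponsor-notification trigger:
- Reword B.10 so that it covers every event that B.5 treats as serious, whatever its causality or expectedness.
- State in B.10 whether AE includes non-serious events. If it does, say which ones and on what form and timescale, consistently with B.5's recording exemption for mild, SPC-listed events.
- In B.10.1 and B.10.2, name the MHRA alongside the REC, as the lead-in does.
- Reconcile OXREC in B.10.2 with the committee named under Ethical approval.

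The cost is a few sentences of appendix wording, submitted to the REC as an amendment. Design, sample size, visits and data collected do not change. The sponsor may receive some additional SAE reports if practice would otherwise have followed B.10 alone.
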